#### Population

We aim to include a diverse population of fifty adults diagnosed with PD or parkinsonism by a neurologist that have both supine hypertension (systolic BP of ≥ 140 mmHg, and/or diastolic BP of ≥ 90 mmHg, after 5 min of supine rest) [12] and orthostatic hypotension (systolic decrease of ≥ 30 mmHg [27] or diastolic decrease of ≥ 10 mmHg upon standing, i.e. the orthostatic hypotension criteria for those with co-existing supine hypertension) [27, 28]. Participants must experience symptoms of orthostatic intolerance (e.g., dizziness, cognitive slowing or blurry vision while standing). Participants must be able to walk, with or without walking aid, must have a stable medication regime for both supine hypertension and orthostatic hypotension during participation, and are not allowed to simultaneously participate in other intervention trials. Finally, participants are only eligible if they can adhere to the study schedule themselves or with help of support at home.

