First, we will plan an in-clinic visit (either at the Radboudumc or LUMC). For consistency, this visit will always be scheduled in the early afternoon. Here, participants can ask additional questions and sign informed consent. The researchers will then gather baseline characteristics, perform their initial assessments with continuous BP measurements and several questionnaires. The assessments and questionnaires can be found in Table 1. Finally, the participant will be asked to install an app through which they can report their at-home measurements.After this session, the participants are randomized to one of the two groups. We will apply the randomization feature of the data management system Castor EDC with block sizes of two and four to allow the interim analysis. We will stratify based on gender. The researchers who perform the assessments and/or are involved in the analyses will remain blinded to the participant allocation during the study. Only the researchers who perform the randomization and deliver the materials at home will know which group the participants are allocated to. We will not inform the participants that we expect that the first angle in the delayed treatment group has no effect on BP regulation, making this a double-blind study.We will schedule an appointment to deliver all study materials within one week after the first session.Participants will perform daily at home measurements of supine BP and their weight. They will be asked to record their measurements in the app.We will schedule four video calls with the participants to discuss potential caveats and supervise the BP standing tests. Participants will also be asked to fill out several questionnaires in the app on this day and to disclose whether they slept in the prescribed angle. During this video check-in we will also guide the initiation of the 24-hour ABPM (Table 1).Participation ends with a follow-up in clinic session, also scheduled in the early afternoon for consistency, where the BP measurements and questionnaires from the first in clinic session are repeated and participants are asked about their experiences. When they want to proceed HUTS, they are offered to keep the materials and to do so under supervision of their primary care physician.

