#### Final analysis

After completion of the study the data will be analyzed according to the intention-to-treat principles. For the main analysis of the overnight BP measured with the 24-hour ABPM in each phase we will use the overnight BP measured in week 1 as baseline to determine the change score. The 1° angle will serve as placebo, and the rest of the HUTS angles are grouped together for overall effectiveness and the increasing angles separately for determining which angle is the most effective for reducing the overnight BP. To estimate the effect of the HUTS angle we will use a linear mixed model with as a dependent variable the change in overnight BP as measured during the 24-hour ABPM, with fixed effects for angle, group and visit and with a random effect for subject. As covariables the baseline BP value, age and disease duration will be used. The within group differences will also be analyzed for all angles with a linear mixed effects model per group. Dependent variables in this calculation are the angle (fixed effect) and subject (random effect). The daytime variation will be calculated in the same way as described for the overnight BP.

The secondary outcome morning supine BP will be analyzed by averaging the three consecutive morning measurements and comparing the 13 timepoints from each phase with the baseline for overall effect, and by comparing each of the three phases to investigate the difference in effect for angles taking into account the time-effect.

Additional explorative analyses based on the per-protocol principles will be performed, this includes the analysis on tolerability of HUTS, baseline characteristics collected at the in-clinic sessions, the results from the PSQI, falls, FES, PDQ-30, HADS and MHC-SF which all will be exploratively analyzed. The tilt table test will be analyzed to investigate the differences between responders and non-responders by looking at the severity of supine hypertension and orthostatic hypotension.

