## Discussion

We present the rationale and design of the Heads-Up trial, a double-blind phase II RCT to determine the potential benefit of different angles of HUTS as a treatment for both supine hypertension and orthostatic hypotension in people with PD and parkinsonism. Although the HUTS concept has been known for almost 80 years, many unknowns persist regarding the efficacy and feasibility. We therefore propose a home-based trial with a strong focus on the implementability.

Although HUTS is perceived as a simple method, there are several practical challenges which we tried to tackle in advance as much as possible. These can be found in the Methods section. The present study also focuses in part on investigating these challenges and hence the tolerability of the HUTS method. It may be difficult to acclimate to sleeping in a tilted position and all the adjustments that need to be made to implement it. The practical application is complex and highly individual, requiring a personalized approach. Measures will be taken to ensure that space or sleeping situations do not lead to an inclusion bias. To ensure this, we will provide each individual participant with all necessary support, including at least one home-visit for installation.

Apart from the practical challenges of the study, there are several important methodological issues. With the specific population studied here it may prove difficult to include a diverse group of participants (e.g., gender or with relation to socio-economic status), as men are more likely to be diagnosed with PD or parkinsonism, and underserved populations (such as those with a migration background) are often not reached. Among persons with PD, autonomic failure usually develops late in the course of the disease. This might impede recruitment due to frailty and abundant physical and cognitive symptoms. However, persons with parkinsonism, specifically those with MSA, often exhibit orthostatic hypotension at an earlier disease stage, sometimes even as the main presenting symptom. Although their disease progression may be faster, we expect that we will be able to recruit more mobile participants among these subgroups. To include underserved populations, we will recruit not only through neurologists in the outpatient clinics of university medical centers, but also in smaller or rural hospitals and clinics. We will also reach out to specialized nurses, physiotherapists, and people with PD themselves through open recruitment.

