Taken together, HUTS is an attractive intervention with the unique potential to positively impact supine hypertension and orthostatic hypotension simultaneously. Although the intervention seems simple and straightforward, the best way to implement in often frail people with movement disorders needs further study. If the current trial proves successful, a definitive phase III RCT will be designed, powered to study clinically relevant outcomes. The current study will help to determine which angles and target population this new trial should focus on. The current work will lay the foundation for practical guidelines for a structured and personalized application of HUTS.

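### The primary model adjusts for disease duration but not for diagnosis, although the trial pools PD with parkinsonism: a possible loss of precision, without bias, and no stated analysis separates the two

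*Protocol article*

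**What the plan says.** All references are to the protocol article.

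- Final analysis: the change in overnight BP is modelled "with fixed effects for angle, group and visit and with a random effect for subject". The covariates follow: "As covariables the baseline BP value, age and disease duration will be used". No diagnosis term and no interaction is listed.
- Population: "We aim to include a diverse population of fifty adults diagnosed with PD or parkinsonism by a neurologist".
- Procedure: "We will stratify based on gender". No other stratification factor is given.
- Discussion, on PD: "Among persons with PD, autonomic failure usually develops late in the course of the disease". On parkinsonism, and MSA in particular: these patients "often exhibit orthostatic hypotension at an earlier disease stage, sometimes even as the main presenting symptom". The authors expect to find more mobile participants among these subgroups.
- Discussion, closing paragraph: the trial will help determine "which angles and target population this new trial should focus on".
- Background and Final analysis: participant characteristics will be explored as predictors, baseline characteristics are listed among the exploratory analyses, and responders will be compared with non-responders on the severity of supine hypertension and orthostatic hypotension. Diagnosis is not named in any of these.

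**The concern.** Eligibility requires symptomatic orthostatic hypotension together with supine hypertension. On the protocol's own account, a PD patient usually reaches that state after a long disease course, while an MSA patient may reach it early. Among those enrolled, disease duration is therefore likely to be entangled with diagnosis. A covariate list with duration as a main effect and no interaction is ordinarily read as one slope for everyone. That slope then has to carry both the effect of duration within a diagnosis and any difference between diagnoses. If the two pull in opposite directions, the covariate explains less than it could.

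Two things are at stake. One is the precision of the between-group estimate, including protection against chance imbalance in a factor that is neither stratified nor adjusted for. The other is what the trial can report about the population for phase III, when the two diagnoses that define eligibility are never compared in a stated analysis.

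**Working it through.** **No stated figure to reproduce.** The article gives no SD, no effect size and no PD/parkinsonism split. Every input below is an assumption, in units of the error SD.

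**1. Loss of precision.** Let q be the parkinsonism share (0.2 or 0.4), duration 12 years (SD 5) in PD and 4 years (SD 2) in parkinsonism, δ the diagnosis effect on the change score, β the effect per within-diagnosis SD of duration (0 or 0.3), and the error variance 1. Baseline BP and age are left out for simplicity.

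- Within-diagnosis variance of duration: W = (1−q)·25 + q·4
- Total variance of duration: V = W + q(1−q)·8²
- Within-diagnosis covariance with outcome: c = β[(1−q)·5 + q·2]
- Total covariance: C = c − q(1−q)·8·δ
- Pooled slope per year: C/V
- Residual variance, duration only: 1 + β² + q(1−q)δ² − C²/V
- Residual variance, diagnosis plus duration: 1 + β² − c²/W

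Worked case, q = 0.4, β = 0.3, δ = 0.8: W = 16.6, V = 31.96, c = 1.14, C = 1.14 − 1.536 = −0.396. Duration only: 1.2436 − 0.0049 = 1.2387, SD 1.113. Diagnosis plus duration: 1.09 − 0.0783 = 1.0117, SD 1.006. Ratio 1.107.

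| q | β | δ | Pooled slope per year | Residual SD ratio |
|---|---|---|---|---|
| 0.4 | 0.3 | 0.8 | −0.012 | 1.107 |
| 0.4 | 0.3 | 0.4 | +0.012 | 1.054 |
| 0.4 | 0.3 | 0 | +0.036 | 1.018 |
| 0.4 | 0.3 | −0.4 | +0.060 | 1.001 |
| 0.4 | 0.3 | −0.8 | +0.084 | 1.004 |
| 0.2 | 0.3 | 0.8 | +0.010 | 1.087 |
| 0.2 | 0.3 | −0.8 | +0.076 | 1.005 |
| 0.4 | 0 | ±0.8 | ∓0.048 | 1.039 |
| either | 0 | 0 | 0 | 1.000 |

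The loss runs from nothing to about 11%. It is sizeable only when the diagnosis effect opposes the duration effect. With β = 0.3 the slope changes sign in one cell only.

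**2. Validity and power.** The first phase (6° versus 1°, 25 per group) was simulated with the plan's covariates, 6,000 runs per scenario, a parkinsonism share of 20% or 40%, and mean durations of 10 and 4 years. Bias stayed within about ±0.01 SD and type I error between 0.045 and 0.052. Power at a true effect of 0.8 SD:

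| Scenario | Plan | Plus diagnosis | Plus diagnosis and diagnosis × duration |
|---|---|---|---|
| Diagnosis irrelevant | 0.76 | 0.75 | 0.74–0.75 |
| Diagnosis effect 0.5 SD, opposite slopes | 0.71–0.72 | 0.74–0.75 | 0.74–0.75 |
| Diagnosis effect 1.0 SD, steeper opposite slopes | 0.63–0.64 | 0.73–0.74 | 0.75 |

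When diagnosis is irrelevant, adding it raises the standard error from 0.289–0.294 to 0.293–0.298, about 1%.

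**3. Chance imbalance.** Under a plain 25:25 split (hypergeometric, ignoring blocks and gender strata), the groups differ by 4 or more parkinsonism patients with probability 0.29 (10 of 50) or 0.39 (20 of 50), and by 6 or more with probability 0.07 or 0.15.

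**4. What a comparison of diagnoses could show.** With nP parkinsonism and nD PD patients, each divided equally between groups, the SE of the between-group interaction is √(4/nP + 4/nD). The difference detectable at 80% power, two-sided 5%, is (1.96 + 0.84) × SE. For nP = 10, SE = √(0.4 + 0.1) = 0.707, giving 1.98 SD. For nP = 25, SE = 0.566, giving 1.58 SD. Power at 0.8 SD is 20% to 29%. For a diagnosis difference in within-subject change the SE is half as large, so 0.79 to 0.99 SD is detectable.

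**The case against.** The strongest reply is that a prespecified covariate set which omits one prognostic factor is valid under randomisation. That stands: a reader might infer that the duration term distorts the treatment estimate, and neither the text nor the simulation supports it. The duration slope is a nuisance coefficient that the article never proposes to interpret, so a change in its sign would defeat no stated aim, and it arises only in a narrow set of assumptions. Nothing in the documents says which way a diagnosis effect would run, and in the reversed direction duration already captures nearly everything. Many angle contrasts are within subject, where a diagnosis main effect largely cancels. All this limits the size of the point.

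A reader might also infer that the target-population question is ignored. That goes too far: the article plans exploratory work on participant and baseline characteristics and on responders. The detail of subgroup analyses may sit in a full protocol or SAP that is not shown. What remains is narrower: none of the analyses that are stated names diagnosis.

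Nor does the Discussion show that MSA patients are sought deliberately. It states an expectation about who can be recruited.

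What the reply does not remove is that the covariate list is a stated choice, that it sits awkwardly with the Discussion's account of the two disease courses, and that the missing factor should be known for every participant from eligibility.

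**Conclusion.** The point holds as a modest matter of efficiency and reporting. The model adjusts for duration without diagnosis in a mixed population, and diagnosis is not a stratification factor. The randomised comparison remains unbiased with its nominal error rate. The possible cost is a residual SD 0% to about 11% larger, or in the simulated scenarios nothing to about 10 power points against a model with diagnosis added, and an imbalance in diagnosis would go unadjusted. These sizes rest on assumed case mix, durations and effects, and on simplified models without the repeated measures. That duration enters with a single slope is inferred from a list without interactions. For phase III, no stated analysis separates PD from parkinsonism, and even a planned comparison could detect only very large between-group differences with 50 participants.

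**What to change.** - Add diagnosis (PD versus parkinsonism, with MSA identified separately if numbers allow) to the covariates of the primary mixed model.
- Fit a diagnosis-by-duration term as a sensitivity analysis. Centring duration within diagnosis is not a substitute: once diagnosis is in the model it is only a reparameterisation, leaves the fit unchanged and keeps one common slope.
- Report the angle effects by diagnosis with confidence intervals, labelled exploratory and descriptive. State that a between-group interaction below about 1.6 to 2.0 SD is unlikely to be detected, so these estimates should not alone decide the phase III population.

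The cost is one or two degrees of freedom, about 1% in the standard error if diagnosis turns out not to matter, and wide subgroup intervals. No new data collection should be needed, since participants enter with one of these diagnoses.

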#### Intervention

All participants in this study are subject to a six-week intervention. They will be sleeping in a whole-body HUTS position at three different angles, for two weeks each. The treatment group will sleep at HUTS angles of 6°, 12° and 18°. The delayed treatment group will first sleep at the placebo angle of 1° which is considered the control, after which they also sleep at 6° and 12° HUTS (Fig. 1). In both groups the intervention is preceded by a week of horizontal sleeping for baseline measurements.

The necessary materials will be delivered to the participants’ homes. To facilitate implementation in the home situation we have developed a frame that can be used to tilt the mattress into all different angles (Fig. 2A). For those who do not wish to use this frame, we offer wedge shaped mattresses with similar HUTS angles (Fig. 2B). The effect of HUTS on sleep quality is not yet known, but higher angles of HUTS may cause discomfort. Slipping can be reduced by increasing the friction of bedcover fabric, placing a rolled-up towel under the hips or in several other ways. We will expand this list as participants figure out what works for them during the study. We offer to provide each participant with a sleeping partner the frame for both so that they can sleep next to each other in the same angle during the trial. For good application of the HUTS method in the participant’s home, we will pay a home visit not only to deliver the materials, but also to offer support. For those who require or request extra help during the study we will provide this by offering a telephone or video call and, if necessary, by additional home visits.

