An additional methodological challenge due to the design of the study is the complexity of the statistical analyses. The order of the angles of the intervention are not randomized, which was chosen due to the impact that the order may have on the perception of the different angles. By increasing the tilt angles step by step, the participants can slowly get used to tilted sleeping. We hope this improves the tolerability of the higher inclinations and reduces dropouts due to uncomfortable sleeping. If they still do not tolerate a new, higher angle, we will ask participants to return to the previous angle. From a physiological perspective one would expect that the impact HUTS will increase proportionally to the size of the angle. Randomizing the order of the angles would require wash-out periods to evaluate the independent effect of each angle but also longer intervention periods for steeper angles to reach a steady state of the effect. We therefore preferred the fixed and incremental order of HUTS inclination as a more practical design. The intention-to-treat analysis is likely to influence our results for the efficacy of the higher angles; we will therefore perform an additional per-protocol analysis.

Orthostatic hypotension often results from multiple contributing factors that can be neurogenic and non-neurogenic. Autonomic dysfunction, nocturnal hypertension, nocturia, hypovolemia, BP medication or dopaminergic medication may all contribute to orthostatic hypotension, but we cannot study each factor separately or their interaction with each other. We will try, however, to identify hemodynamic markers to predict HUTS efficacy. We will also monitor the impact of HUTS on nocturia, an often neglected and incapacitating symptom in PD or parkinsonism. Interestingly, nocturia seems more prominent in persons with supine hypertension and may contribute to orthostatic intolerance, but no concise evidence exists [17]. By monitoring nocturia and including those with supine hypertension and orthostatic hypotension, we hope to uncover the complex interplay between these factors.

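### Within each group, angle and study phase are the same factor, so the per-group mixed model reports angle effect plus any change over time

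*Protocol article*

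**What the plan says.** The protocol article's Final analysis section describes two models for the change in overnight blood pressure from the horizontal week.

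- The main model pools the groups, "with fixed effects for angle, group and visit and with a random effect for subject", with baseline blood pressure, age and disease duration as covariates.
- After that: "The within group differences will also be analyzed for all angles with a linear mixed effects model per group". Its terms follow: "Dependent variables in this calculation are the angle (fixed effect) and subject (random effect". These are explanatory terms, so calling them dependent variables is a slip. No visit, phase or time term is named.

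On daytime blood pressure the section says: "The daytime variation will be calculated in the same way as described for the overnight BP".

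The Intervention section fixes the sequences. For one group: "The treatment group will sleep at HUTS angles of 6°, 12° and 18" degrees. For the other: "The delayed treatment group will first sleep at the placebo angle of 1° which is considered the control, after which they also sleep at 6°"; its last angle is 12°. Each angle is kept for two weeks. The Outcome measures section places one 24-hour recording near the end of each phase, which gives three change scores per participant. The Discussion confirms: "The order of the angles of the intervention are not randomized".

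**The concern.** A model with only angle and subject, fitted in one group, compares each participant with himself or herself at successive times. If blood pressure moves over the six weeks for any reason other than the angle, that movement goes into the angle coefficients.

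The plan allows for time elsewhere: visit is in the main model, and the morning supine analysis is to take a time effect into account. The Discussion adds that randomising the order would have required wash-out, and longer periods at steeper angles to reach a steady state. The per-group model has no such protection.

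It concerns the primary outcome and would yield an orderly series of angle estimates. The Discussion says the trial should help decide which angles a phase III trial focuses on. A dose-response that is partly or wholly a time trend would be poor evidence for that choice. The staggered randomisation already offers better evidence, because in every phase the two groups sleep one angle step apart at the same time. The per-group model does not use it.

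**Working it through.** **Inputs from the protocol article.** Sequences 6°-12°-18° and 1°-6°-12°; one recording per phase; intention-to-treat, so angle is taken as assigned; 50 participants, hence about 25 per group. No SD, significance level or expected drift is stated, so there is no figure of the plan's own to reproduce.

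**Step 1: can angle and time be separated within a group?** Count the columns and the rank of the fixed-effects design (intercept plus indicator columns) over the group-by-phase cells.

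| Data | Terms | Columns | Rank |
|---|---|---|---|
| Either group alone | angle | 3 | 3 |
| Either group alone | visit | 3 | 3 |
| Either group alone | angle + visit | 5 | 3 |
| Both groups | angle + visit | 6 | 6 |

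Angle and visit span the same space within a group. Adding visit there contributes nothing that can be estimated. The cause is the fixed order, not a forgotten covariate. Separation needs both groups together.

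**Step 2: size of the bias.** Let there be no angle effect and a shared change of d mmHg per phase. The expected changes from baseline are:

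| Phase | Treatment group | Delayed group | Same-visit difference |
|---|---|---|---|
| Weeks 2-3 | 6°: d | 1°: d | 0 |
| Weeks 4-5 | 12°: 2d | 6°: 2d | 0 |
| Weeks 6-7 | 18°: 3d | 12°: 3d | 0 |

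The per-group contrast 18° v 6° is 3d − d = 2d. With d = −2 mmHg it is −4 mmHg, although the angle does nothing. This identity needs no SD. The between-group difference within a visit stays at zero.

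**Step 3: false-positive rate.** Assumptions, not from the documents: 25 per group, residual SD s of 8, 10 or 12 mmHg, linear drift, 5% test of the angle factor. In the balanced random-intercept model the F test has 2 and 48 degrees of freedom. Under drift its noncentrality is λ = 25 × (d² + 0 + d²) / s² = 50d²/s².

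| Drift per phase | s = 8 | s = 10 | s = 12 |
|---|---|---|---|
| 0 | 5% | 5% | 5% |
| 1 mmHg | λ = 0.78: 11% | λ = 0.50: 9% | λ = 0.35: 8% |
| 2 mmHg | λ = 3.13: 32% | λ = 2.00: 21% | λ = 1.39: 16% |

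Simulation under the same assumptions agrees to within about one percentage point. There the same-visit comparison in weeks 4-5 kept a rate of about 5% at every drift.

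**The case against.** **The model is supplementary.** The Final analysis section gives the question of the most effective angle to the main analysis, and introduces the per-group model afterwards as an addition. It states no test, significance level or decision rule for it. This stands. A reader might infer that the phase III angle will be picked from the per-group results; no passage says so, and the Discussion speaks of the study as a whole. Whether the main model can itself be estimated as worded is a separate question that this point does not rest on.

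**The order is disclosed and justified.** "The order of the angles of the intervention are not randomized, which was chosen due to the impact that the order may have" on how the angles are perceived, and stepwise increase is meant to help tolerability. This is a fair reason for the design. The Discussion does not go on to say that within-group angle contrasts carry time with them.

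**The drift is assumed.** This stands too. The horizontal week with its own recording absorbs part of any habituation, and nothing in the documents shows a steady fall of 2 mmHg per phase. A reader might also blame carry-over and build-up for the false positives. Both are effects of tilt and vanish if tilt does nothing. They can distort a comparison of angles, but they cannot produce the rates in step 3.

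**The groups would not truly replicate each other.** A reader might infer that shared drift makes the two groups look like independent confirmations. Only the steps would agree. The same angle would give different values (6° shows d in one group and 2d in the other), and 6° would equal the 1° placebo in weeks 2-3. Set side by side, the estimates would hint at drift, though imprecisely.

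**Angle as actually slept.** Participants who do not tolerate an angle return to the previous one. Coding the angle actually slept would break the exact overlap, but only through a self-selected subset, and it departs from intention-to-treat.

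**Daytime blood pressure.** That the per-group model is repeated there is the natural reading, not an explicit statement.

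**Conclusion.** The point holds as a limited one that should be corrected. As specified, the per-group angle contrasts estimate angle effect plus time effect, and no further detail in an analysis plan could separate them within one group. This follows from the fixed sequences alone and needs no numerical assumption.

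The practical size depends on drift, which is unknown. The bias in 18° v 6° is twice the change per phase. The false-positive rate is the nominal 5% with no drift, about 8 to 11% at 1 mmHg and about 16 to 32% at 2 mmHg, given 25 per group and a residual SD of 8 to 12 mmHg. These rates illustrate and do not predict.

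The documents do not support the conclusion that the trial's main result is invalid. The randomised comparison of 6° with 1° in weeks 2-3 is untouched.

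**What to change.** 1. Report the per-group course over the phases descriptively, as means with confidence intervals labelled as angle plus time. State that the two cannot be separated within a group, and do not use these results to rank angles.
2. Base angle inference on same-visit contrasts between the randomised groups, adjusted for baseline blood pressure: 6° v 1° in weeks 2-3, 12° v 6° in weeks 4-5, 18° v 12° in weeks 6-7.
3. State that only the first contrast is free of differing earlier tilt exposure. The later two compare the randomised sequences, and read as pure angle steps they assume no carry-over.
4. Say explicitly whether daytime blood pressure follows the same rules, and correct the term for the explanatory variables.

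The cost is wording and analysis only, with no new data or participants. Precision falls somewhat. With an assumed between-person SD of 8 and residual SD of 10 mmHg, before baseline adjustment, the standard error of one step is √(2 × (8² + 10²) / 25) ≈ 3.6 mmHg between groups, against √(2 × 10² / 25) ≈ 2.8 mmHg within a group.
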